## Abstract

**Background:**

In the patient-centered medical home model of health care, both health care providers (HCPs) and patients must understand their respective roles and responsibilities, view the other as a partner, and use communication skills that promote shared decision making. This is particularly necessary in chronic conditions where outcomes depend on behavior change and in underserved populations where the burden of chronic disease is high.

**Objective:**

The objectives of this study are to determine if a Patient Empowerment Program (PEP) (1) is acceptable to patients and feasible across multiple clinical sites; (2) will increase patient preference for control in medical decision making, improve patient perceptions of patient-HCP communication, and increase patient activation; (3) is associated with an increase in diabetes self-management behaviors; and (4) has an effect on hemoglobin A
_1c_(HbA
_1c_) level.

**Methods:**

This study recruited English-speaking adult patients with type 2 diabetes mellitus from three urban clinical sites in New York City and randomized them to an immediate intervention group that completed the PEP intervention or a deferred intervention group that served as a wait-list control and completed the PEP intervention after 3-4 months. The PEP intervention consists of two facilitated small group sessions. Session 1 focuses on defining HCP and patient roles in the medical encounter by introducing ideal communication behaviors in each role and by providing both positive and negative examples of patient-HCP encounters. Session 2 focuses on practicing communication skills by role-playing with actors who serve as standardized health care providers. After the role play, participants set goals for their own health care and for future interactions with their HCPs. Outcome measures include the Patient Activation Measure; Ask, Understand, Remember Assessment; Krantz Health Opinion Survey; SF-12v2 Health Survey; Diabetes Self-Management Questionnaire; and HbA
_1c_. These measures will be assessed at the time of enrollment, after the waiting period (deferred intervention only), and then postintervention at 1 week, 3 months, and 6 months.

**Results:**

Study recruitment occurred from November 2014 to June 2015, with a total of 80 patients enrolled. To date, 45 participants have attended at least one session of the PEP intervention. Further intervention sessions and post-intervention follow-up are ongoing, with data collection set to be completed in April 2016 and results of data analysis available by June 2016.

**Conclusions:**

From preliminary participant self-report data, our PEP intervention is acceptable to low-income, low–health literate patients and feasible to hold across multiple clinical sites. Participants have reported learning specific ways to change their behaviors at their next HCP visit (eg, stating their opinions, asking more questions). With the forthcoming quantitative data on participant attitudinal and behavior change, the PEP intervention may ultimately empower participants within the medical encounter and improve health outcomes.

## Introduction

### Background

More than 25.8 million Americans have type 2 diabetes mellitus (T2DM). In 2012, T2DM cost the United States $245 billion in both direct and indirect medical costs [
1]. Comparable to the general population, it has been estimated that 10% of the New York City population suffers from T2DM, and patients with diabetes-related disorders occupy half of the hospital beds in the city [
2]. The patient-centered medical home (PCMH) model, which strives to provide comprehensive care and improve patient’s self-management skills through increasing engagement with health care providers (HCPs), is ideally suited for T2DM care [
3-
5].

Preparing patients for the PCMH model is challenging because of the inherent power differential between HCPs and patients. Efforts to prepare HCPs to practice in the PCMH model have included strategies for encouraging patient self-care activities and behavior change (eg, tailoring, brief negotiation, motivational interviewing) [
6,
7]. Interventions have also been developed to educate patients about disease management and increase involvement in their care [
8-
11]. However, both approaches fail to address the inherent asymmetry in the power dynamics of the physician-patient relationship [
12-
21]. Increasing patient activation is one method that has been suggested to overcome these barriers. Activated patients are knowledgeable about their health conditions, confident in their ability to manage these conditions, and maintain their health by seeking information and performing health promoting behaviors [
22]. In general, more activated patients, as determined by a higher score on the Patient Activation Measure (PAM) [
22,
23], ask more questions during HCP visits [
22-
24] and perform more self-management behaviors including diet and exercise [
22,
23,
25-
28]. More specifically, patients with T2DM who have higher PAM scores report less difficulty in managing their diabetes than those with lower scores [
28]. Furthermore, several interventions that increase patient activation have shown promise for improving outcomes [
29-
32], most notably in congestive heart failure [
29] and T2DM [
30].

Standardized patient (SP) training, a well-established, performance-based intervention, offers a compelling method of activating patients to become partners in their health care. Standardized patients are trained to reliably and validly assess HCP clinical competence [
33-
37] and, as a result, become more activated “real” patients who have higher expectations of HCPs and improved communication with HCPs [
38-
43]. Additionally, SPs have improved their own health behaviors in terms of weight loss [
44] as well as HIV testing and sexually transmitted disease prophylaxis [
45]. More recently, these same training methods have been used to train standardized health care providers (SHPs) to assess communication between HCPs of different disciplines (eg, doctors and nurses) as part of interprofessional education [
46-
48].

Our Patient Empowerment Program (PEP) seeks to adapt the successful SP methodology currently used in HCP education and translate it onto the patient side of the medical encounter [
49]. To do so, the PEP incorporates ideas of shared decision making (SDM), involves role-playing, and helps patients develop the skills to give effective feedback to HCPs using validated checklists of observable behaviors. This intervention is both evidence based and theory supported and addresses the needs of multiple stakeholders, including health system quality leaders, HCPs, patient advocates, SP trainers, and patients. We focus on patients with T2DM because of its high prevalence in the population, the need for frequent contact with the health care system, and the numerous aspects of treatment (eg, lifestyle changes, medications, blood glucose monitoring, annual screenings, and so on) that patients must discuss with their HCPs.

### Objectives

The objectives of this study are to (1) assess the acceptability and feasibility of implementing the PEP across three urban clinical sites; (2) determine if a PEP will change patient preference for control in medical decision making, improve patient self-efficacy in patient-HCP communication, and increase patient activation; (3) determine if participation in the PEP is associated with an increase in diabetes self-management behaviors; and (4) explore the effect of the PEP on hemoglobin A
_1c_(HbA
_1c_) level.

## Methods

### Overview

The PEP is a randomized, wait-list control study (see
Multimedia Appendix 1) that aims to enhance general communication skills so that patients can participate in SDM during office visits, become activated in their own health care, and better manage their medical conditions.

Patients were recruited in cohorts of 20 and then randomly assigned to attend the PEP intervention immediately (immediate intervention) or after a waiting period (deferred intervention). All participants completed a baseline assessment at the time of enrollment (T0) and will complete follow-up assessments 1 week (T2), 3 months (T3), and 6 months (T4) after completion of the PEP intervention (see
Figure 1). Additionally, the deferred intervention group was assessed at the end of the waiting period (T1), immediately before being invited to attend the PEP intervention. The T1 assessment for the deferred intervention group was approximately 3-4 months after randomization and was timed to coincide with the T3 assessment of the immediate intervention group. A wait-list control design was chosen to create a control group with multiple time points of data collection (deferred intervention T0-T1) while still allowing for all participants who enrolled in the study to complete the PEP intervention and post-PEP follow-ups.

Aside from attending the PEP intervention, all participants continued to receive their usual care, including all scheduled primary care and specialty clinic appointments, HbA
_1c_monitoring, and all medications as directed by their physicians.

**Figure 1 figure1:**
[figure not shown]
CONSORT flow diagram. HbA1c: hemoglobin A1c; PEP: Patient Empowerment Program; T2DM: type 2 diabetes mellitus.

### Setting

Bellevue Hospital Center, Gouverneur Health, and Woodhull Medical Center are all within the Health and Hospitals Corporation, a large public hospital system in New York City. The adult ambulatory care clinics at these sites serve patients from the local community as well as immigrants from around the world, with English, Spanish, Mandarin, Cantonese, and Bengali among the most common languages spoken. Approximately one-third of patients have Medicaid or are without health insurance and the most common diagnoses in the clinic include obesity, hypertension, heart disease, diabetes, and asthma.

### Participants

We recruited patients with T2DM who presented to the adult ambulatory care clinic at each site. Patients eligible for inclusion in the study (1) were at least 18 years old, (2) had a diagnosis of T2DM for at least 1 year, and (3) their most recent HbA
_1c_level was between 6.5% and 11%. Patients were excluded if they (1) were unable to speak English or (2) had a major psychiatric illness that impaired their ability to care for themselves (eg, schizophrenia, uncontrolled bipolar disorder, or uncontrolled depressive disorder).

### Recruitment, Randomization, and Retention

Research assistants (RAs) screened all of the clinic appointments each day to identify patients who were eligible for the study. Research assistants then briefly explained the study to all eligible patients who came to their appointment and obtained informed consent from those who decided to enroll (see
Figure 1). After obtaining informed consent, RAs read participants a set of questionnaires to complete the initial (T0) assessment (see
Table 1).

After 20 participants were enrolled in the study, a Web-based random number generator was used to generate a list of 20 integers between one and two. The list was refreshed until it contained 10 ones and 10 twos. Based on this list, participants were assigned in order of their study identification number to the immediate intervention (1) or deferred intervention (2) group. All participants in the immediate intervention group were contacted by phone to schedule the PEP intervention sessions and all participants in the deferred intervention group were contacted by phone and informed that they would be recontacted in 3-4 months to schedule their PEP intervention sessions.

Participants were compensated for participating in the study. They received US $10 and a MetroCard with US $10 at each of the two PEP intervention sessions. They also received US $60 and a MetroCard with US $10 for completing the study if they attended a post-PEP focus group.

In order to increase retention of deferred intervention participants, they received a letter from our program and an educational handout about T2DM in the mail approximately every 3 weeks. Handouts were sent in the same order and all handouts came from the Diabetes Care and Education website [
50]. In total there were four mailings: (1) Nutrition to Help Manage your Diabetes and Weight, (2) Eating Healthy on a Lean Budget, (3) Know Your Blood Sugar Numbers, and (4) Managing and Preventing Hypoglycemia. All four of these handouts were short, only 1-2 pages in length, and contained general information about T2DM that participants should have already obtained from their HCPs as part of their routine treatment. Therefore, we do not expect that receiving these handouts will cause a significant difference in the two randomized groups or otherwise affect the results of the study.

### Outcome Measures

Outcome measures for the study primarily consist of self-report questionnaires assessing health attitudes and behaviors (see
Table 1). Because of the low literacy of the patient population, RAs read all questionnaires to the participants and then recorded their responses. All questionnaires were asked in the same order and a standardized protocol was created so that all RAs asked and clarified questions in the same manner. Outcome measures were assessed at the time of enrollment (T0), after the waiting period (T1: deferred intervention group only), and postintervention after 1 week (T2), 3 months (T3), and 6 months (T4).

**Table 1 table1:** Data collection.

Domain	Measures	Timing of assessment			
		Enrollment (T0)	After waiting period (T1) ( *deferred only*)	1 week after PEP ^a^ (T2)	3 and 6 months after PEP (T3, T4)
Demographics	Age, sex Race and ethnicity Education level Annual income	X			
Clinical characteristics	Number of years with diabetes Current diabetes treatment	X			
Health literacy	Newest Vital Sign [ 51- 53]	X			
Patient activation	Patient Activation Measure [ 23]	X	X	X	X
Ability to obtain information from HCPs ^a^	Ask, Understand, Remember Assessment [ 54]	X	X	X	X
Preference for control in medical decision making	Krantz Health Opinion Survey [ 55]	X	X	X	X
	Preference Control Scale [ 56]	X	X	X	X
Disease management	Diabetes Self-Management Questionnaire [ 57]	X	X		X
Health quality of life	SF-12v2 Health Survey [ 58]	X	X		X
Biological marker of disease severity	Hemoglobin A _1c_	X	X		X
PEP intervention feedback	Qualitative data analysis of focus group discussion			X	

^a^PEP: Patient Empowerment Program; HCP: health care provider.

#### Primary Outcome

The primary outcome of the study is patient activation, as measured by the short form of the PAM [
23]. The PAM is a 13-item interval level, unidimensional, Guttman-like scale with four response options, ranging from 1 = disagree strongly to 4 = agree strongly. It has been validated across multiple patient populations and has been shown to be reliable, with Rasch person reliability estimates ranging from .73-.84. The overall score on the PAM ranges from 0-100 and PAM scores can be categorized into four levels of activation. In level one, the lowest level, patients believe taking an active role in their health is important but are unprepared for this role. In level two, patients have some knowledge but still struggle to manage their medical conditions. In level three, patients begin to take action in terms of self-management but do not have the skills to support or sustain their behavior. Finally, in level four, patients have adopted self-management behaviors and work on maintaining them in stressful life situations [
23,
30].

57]. The DSMQ is a 16-item interval level scale with four response options that range from 0 = does not apply to me to 3 = applies to me very much. It includes a Summary Scale as well as four subscales: Glucose Management, Dietary Control, Physical Activity, and Health-Care Use. The DSMQ was validated against a longer diabetes self-care scale and has been shown to significantly correlate with HbA
_1c_. It also has good internal consistency reliability, with Cronbach’s alpha = .60-.84.

#### Exploratory Outcome

HbA
_1c_will serve as an exploratory outcome for the study. HbA
_1c_is exploratory for this study because participants did not undergo HbA
_1c_testing at specific times during the study period. Rather, participants will continue to have HbA
_1c_levels monitored as part of their routine care and the HbA
_1c_closest to enrollment (T0) and each follow-up time point (T1, T3, and T4) will be collected from the electronic medical record (EMR) and used for data analysis. Therefore, it is possible that a significant number of follow-up HbA
_1c_values may be missing or not collected at the time of follow-up and those that are will not correlate precisely to the same time period as the questionnaires.

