### Data Analysis

First, descriptive statistics including mean, standard deviation, range, skewness, and kurtosis for all continuous variables as well as frequencies for all categorical variables will be calculated at each time point (T0-T4). Because of concerns about the relatively small sample size and low literacy/health literacy, the normality of all continuous variables will be assessed both graphically with histograms as well as statistically using the Shapiro-Wilk and Kolmogorov-Smirnov tests, and transformations will be made if necessary. Then we will assess for any baseline (T0) differences between two separate groups: (1) the randomly determined immediate intervention and deferred intervention groups and (2) all participants who attended the PEP intervention and those who did not. Both of these analyses will be conducted using chi-square test for categorical variables and either independent samples
*t*test or Wilcoxon rank sum test for continuous variables.

Next, analyses will be conducted within each intervention group to evaluate for any effect of the PEP intervention on the primary, secondary, and exploratory outcomes using chi-square test for categorical variables (eg, PAM level, PCS) and either repeated-measures
*t*test or Wilcoxon signed rank test for continuous variables (eg, PAM score, AURA, Krantz, SF-12v2 Health Survey, DSMQ, and HbA
_1c_). Initial assessment (T0) will be compared with each of the post-PEP assessments (T2-T4) for each variable. For the deferred intervention group, initial assessment (T0) will be compared with the assessment at the end of the waiting period (T1), which will then be compared with each post-PEP assessment (T2-T4).

After analyzing each group individually, the groups will be combined in order to have a larger sample size for pre- and post-PEP comparisons. Pre-PEP intervention data for these analyses will consist of data from enrollment (T0) for participants in the immediate intervention group and data collected at the end of the waiting period (T1) for participants in the deferred intervention group. Repeated-measures analyses will be conducted on the primary, secondary, and exploratory outcomes as described above and pre-PEP data (either T0 or T1) will be compared with each post-PEP assessment (T2-T3).

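### HbA1c is both an entry criterion and an outcome, so zero change from T0 is not the no-effect null in its pre-post tests; the sign and size of the bias cannot be settled from the protocol

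*Protocol article*

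**What the plan says.** Under Participants, the most recent HbA1c must satisfy the condition that the "level was between 6.5% and 11" percent.

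Under Exploratory Outcome, HbA1c "will serve as an exploratory outcome for the study". The reason given is that participants had no HbA1c "testing at specific times during the study period". Routine-care values are used instead: those "closest to enrollment (T0) and each follow-up time point (T1, T3, and T4) will be collected from the electronic medical record (EMR"). The section warns that follow-up values may be missing or mistimed. It does not mention that the baseline has been selected.

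Under Data Analysis, "analyses will be conducted within each intervention group to evaluate for any effect of the PEP intervention on the primary, secondary, and exploratory outcomes", with HbA1c named among the variables for the paired t or signed rank test. "Initial assessment (T0) will be compared with each of the post-PEP assessments (T2-T4) for each variable"; by Table 1 this means T3 and T4 for HbA1c. The deferred group is also tested T0 against T1, and T1 against post-PEP. In the pooled analysis the pre-PEP value differs by arm, T0 for immediate and T1 for deferred: "data from enrollment (T0) for participants in the immediate intervention group and data collected at the end of the waiting period (T1) for participants in" (quote cut before the second arm is named).

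No between-group test of change is described. The mixed models list group and time but no group-by-time term.

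**The concern.** A paired test takes zero mean change as its null. That matches the absence of a PEP effect only if baseline and follow-up would have the same mean without PEP. Here the baseline may be the reading that had to fall inside the window, while the later readings were free to fall anywhere. Regression to the mean then produces a change that has nothing to do with PEP. Perfectly timed readings would not remove it. HbA1c is the only outcome that is also an entry criterion, so the problem is confined to objective 4. What is at stake is whether an HbA1c change in the immediate group, or in the pooled sample, is wrongly credited to PEP or wrongly masks an effect.

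**Working it through.** **1. The plan's own figure.** The only sample-size figure is for PAM: d = 0.48, alpha .05 (two-sided assumed), power 0.80, n = 36.
- Normal approximation: ((1.960 + 0.8416)/0.48)² = 34.07, so 35.
- Exact paired t: 36.03; power at n = 36 is 0.7996.
- A two-group comparison would need 69 per arm.

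So 36 reproduces as a single-group pre-post calculation, which shows where the planned inference lies. No figure is given for HbA1c.

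**2. Formula.** Let X be the qualifying reading used as T0 and Y a later reading, with the same clinic mean µ and SD σ, correlation r, and no PEP effect. With linear regression of Y on X,

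E[Y − X | 6.5 ≤ X ≤ 11] = (1 − r)(µ − m), where m is the mean of X inside the window.

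For a normal distribution, m = µ + σ[φ(a) − φ(b)]/[Φ(b) − Φ(a)], with a = (6.5 − µ)/σ and b = (11 − µ)/σ.

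**3. Normal model.** µ, σ and r are assumptions; the window is from Participants.

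| µ | σ | m | r | (1 − r)(µ − m) |
|---|---|---|---|---|
| 7.4 | 2.0 | 8.28 | 0.60 | 0.40 × (−0.88) = −0.35 |
| 7.4 | 1.5 | 8.05 | 0.75 | 0.25 × (−0.65) = −0.16 |
| 8.2 | 1.5 | 8.45 | 0.75 | 0.25 × (−0.25) = −0.06 |
| 8.75 | any | 8.75 | any | 0 |
| 9.0 | 2.0 | 8.84 | 0.60 | 0.40 × 0.16 = +0.06 |

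The change looks like improvement when µ is below m, is nil at the window's midpoint of 8.75, and looks like worsening above that.

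**4. Skewed model.** The linear formula no longer holds, so this was simulated with shifted-lognormal readings (shift 4). Over µ 7.4-8.2, σ 1.5-2.0 and r 0.6-0.75 the no-effect change is −0.13 to +0.07. In the skewed models the sign turns at a clinic mean of about 8%.

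**5. False improvement rate** (nominal 2.5% in that tail, no PEP effect, every T0 the qualifying reading, r 0.6-0.9). The n = 20 column is half of the 40-completer goal.

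| Clinic mean | Normal, n = 20 | Normal, n = 36 | Skewed (SD 1.8), n = 36 |
|---|---|---|---|
| 7.5 | 6-13% | 7-20% | 4-7% |
| 8.0 | 4-7% | 5-10% | 2-3% |
| 8.5 | 3-4% | 3-4% | 1-2% (false worsening 4-6%) |

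**6. Which tests carry the bias.**
- Within-group T0 versus T3 or T4: in full, times the fraction of T0 values that are the qualifying reading. If half are fresh, −0.35 to −0.06 becomes about −0.18 to −0.03.
- Pooled test: only the immediate group's share. With equal groups the bias halves; at mean 7.5 and n = 36 it is −0.03 to −0.16, with a false improvement rate of 5-8%.
- Deferred T1 versus post-PEP: zero in this model, because T1 is not screened.

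**7. The concurrent contrast.** The Overview times the deferred T1 to coincide with the immediate T3. With a PEP effect δ, the expected immediate T0-T3 change is δ + (1 − r)(µ − m), and the expected deferred T0-T1 change is (1 − r)(µ − m). The difference is δ.

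**The case against.** The strongest reply is that this is a small matter on an outcome the protocol already calls exploratory, with its data limitations declared. The primary outcome and the sample size do not depend on it. Closest to enrollment is not the same as last before enrollment, and patients enrolled at clinic appointments, so some T0 values will be fresh. All of this stands, and it limits both size and consequence. It does not restore a valid null for the T0-based tests, and the declared limitations concern missing and mistimed values, not selection.

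Three stronger readings are tempting and are not supported.
- **That a fall in HbA1c is to be expected from selection.** The window cuts both tails, and the documents give no clinic mean, SD, shape or correlation. Under a skewed model the sign changes within the assumed range of means.
- **That all HbA1c pre-post tests are compromised.** The deferred T1-based tests, already planned, are not, and the pooled test is only partly affected.
- **That an earlier EMR reading would be a clean baseline.** This works only if readings correlate equally however far apart they are. If the earlier reading correlates 0.75 with the qualifying one but 0.60 with a later follow-up, then at mean 7.4 and SD 2.0 the residue is (0.60 − 0.75) × (8.28 − 7.4) = −0.13. It also lengthens the pre-post interval and may be unavailable in this record system.

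**Conclusion.** The point holds for the within-group T0-based HbA1c tests and for the immediate group's share of the pooled test: their null is not the null of no PEP effect, and no analysis stated in the article corrects this. The size is an assumption throughout. For clinic means of 7.4-8.2%, SD 1.5-2.0 and correlation 0.6-0.75, if T0 is the qualifying reading, it is about −0.35 to −0.06 points (normal) or −0.13 to +0.07 (skewed). A reader might infer that any HbA1c improvement seen would be an artefact; the documents support only that a T0-based change cannot be told apart from one. The consequence is limited to how exploratory objective 4 is read.

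**What to change.** For HbA1c only:

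1. Report T0-based within-group and pooled changes as descriptive, stating that they include regression to the mean, and not as evidence of a PEP effect.
2. Base the HbA1c conclusion on the immediate T0-T3 change against the deferred T0-T1 change, or on a group-by-time term in the mixed model. For the latter, code time from randomization so that immediate T3 and deferred T1 share a time point.
3. Analyze patients in their randomized arm, including the 11 moved from immediate to deferred. Their HbA1c at the T1 time point can be sought in the EMR whether or not they completed the T1 questionnaires (6 did).
4. Keep deferred T0-T1 as the control interval, and do not substitute an earlier EMR reading for the baseline.

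No new visits or patients are needed. The cost is precision. With a common SD of change s, a pooled test on 40 pairs has standard error s/√40 = 0.16s. The between-arm contrast has s√(2/20) = 0.32s with 20 per arm, or s√(2/40) = 0.22s if all 40 randomized per arm (80 enrolled, allocated 10:10 per cohort) have EMR values. That is about 2 or 1.4 times as wide, which is acceptable for an exploratory outcome.
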